### Methods for additional analyses (e.g. subgroup analyses) {20b}

An economic evaluation taking the form of a cost-effectiveness analysis (CEA) will be conducted to compare the efficiency of spironolactone and cycline treatment. The analysis will be conducted from the societal perspective, which means that costs to hospitals, the National Health Insurance System and patients will be considered, over a 6-month time horizon, to be consistent with the primary endpoint. The main judgement criterion will be the incremental cost-effectiveness ratio defined as a cost per QALY gained. To estimate QALYs, patients will be asked to fill in the EuroQol EQ-5D health-related quality of life questionnaire.

For the estimation of costs, resources consumed will be recorded prospectively in the patient’s diary for a period of 6 months following the start of the treatment. The main resources to be collected are in the patient diary are: * Medication * Ambulatory physician visits * Dermocosmetic care.

Unit costs will be estimated using conventional tariffs from the French National Health Insurance System to value ambulatory care consumption. Costs in each arm will be estimated by multiplying the amount of each type of resource consumed by their corresponding unit monetary value. In CEA, the outcomes of an intervention are evaluated in terms of the QALY, which is a numerical composite measure that encompasses information about the length of life and the health-related quality of life. They are computed by weighting each year by a corresponding quality of life factor, usually ranging from 0 (death) to 1 (perfect health). Quality of life weights will be obtained by asking patients to answer the EuroQol EQ-5D quality of life questionnaire at baseline and at 2, 4, and 6 months from baseline. The difference in QALYs between the two arms of the study will be calculated using analysis of area under the curve, with linear interpolation of utility scores between measurement time points.

The EQ-5D will also be applied at 9 and 12 months to evaluate quality of life up to M12, as a secondary objective, independently from the cost-effective analysis. The ICER (see below) comparing the spironolactone and cycline arms will be analysed using a non-parametric bootstrap approach to produce estimated confidence intervals at 95% over the mean ICER:

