### Methods in analysis to handle protocol non-adherence and any statistical methods to handle missing data {20c}

All participants will receive the assigned study treatment until unacceptable toxicity, death, loss to follow up, withdrawal of consent or termination of the study by the Sponsor, in accordance with local standards of care. Unacceptable toxicity and death will be considered as failure for the primary criteria analysis. Loss to follow up, missing data for the primary criteria and early termination of the study by the Sponsor will be also considered as failures by the ITTm and not replaced.

Patients who did not fulfil the inclusion criteria after randomization and those who never began their treatment will be replaced. For the clinical secondary criteria analysis, patients with missing data will be withdrawn. Missing data in cost-effectiveness analysis will be handled according to a multiple imputation method in the ITTm sample. If a patient is released from the study (e.g. in the event of adverse reactions (ARs) preventing the continuation of the study), her data will not be collected, except for safety data (follow up of ARs or onset of ARs associated with the experimental treatment, based on pharmacokinetic data).

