### Adverse event reporting and harms {22}

Side effects reported in clinical trials and case series with spironolactone and the management of acne in women [22] are as follows: (1) the most common side effect in both the clinical trials and case series was menstrual irregularities: 38/264 (14.4%) in the clinical trials and 216/543 (39.8%) in the case series. Thee was no side effect apart from menstrual disturbances with an incidence above 5% in the randomized clinical trials or case series; (2) uncommon side effects (0.1–1.0%) were postural hypotension, depression, diarrhea, muscle pain, increased appetite, drowsiness, rashes/drug eruptions, chloasma-like skin pigmentation, polydipsia, weakness, edema of the legs, change in libido and palpitations. No women were reported to have elevated levels of potassium, and a recent multicentre study of 974 women [52] concluded that routine monitoring of serum potassium in healthy women taking spironolactone for acne is not necessary. Some investigators mentioned that certain side effects were considered beneficial: breast enlargement, reduced symptoms of premenstrual syndrome and less greasy skin and hair. The most frequent adverse reactions to cyclines are photosensitization, gastrointestinal disorders including gastric or esophageal pain, and nausea/vomiting*.*

Any adverse event, whether expected or unexpected, serious or not, must be collected real-time in the study eCRF. All SAEs, whether expected or unexpected, must be reported immediately (on the day of the investigator becoming aware of the event) to the Sponsor through the eCRF. The information mentioned on this form and on attached documents must be complete, accurate, clear (no abbreviations) and coded. Pregnancy, overdose, misuse, medication errors or potential medication errors and quality defects should be notified by the investigator to the Sponsor even if there is no associated adverse reaction.

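### Women released before month 6 leave no observed costs or EQ-5D for the 6-month cost-effectiveness analysis, and safety data after release are narrower than the adverse-event endpoint

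*Protocol article*

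**What the plan says.** All references are to the protocol article.

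- **Data after release, {20c}.** When a woman is released from the study, "her data will not be collected, except for safety data". The example of a reason for release is "in the event of adverse reactions (ARs) preventing the continuation of the study". The safety data that continue are described as "follow up of ARs or onset of ARs associated with the experimental treatment, based on pharmacokinetic data".
- **Missing economic data, {20c}.** "Missing data in cost-effectiveness analysis will be handled according to a multiple imputation method in the ITTm sample".
- **Economic evaluation, {20b}.** "The analysis will be conducted from the societal perspective", with a 6-month horizon. Resource use is kept in a patient diary "for a period of 6 months following the start of the treatment", and utilities come from EQ-5D at baseline, M2, M4 and M6. No exception is made for released women. The section also promises a sensitivity analysis for the ICER, without describing it.
- **Safety endpoint, {12}, and reporting rule, {22}.** The endpoint counts all AEs and SAEs to month 12. The reporting rule is "Any adverse event, whether expected or unexpected, serious or not, must be collected real-time in the study eCRF". Neither is limited by arm or by attribution.
- **Primary endpoint, {20c}.** Toxicity, death, loss to follow-up and missing values all count as failure.

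**The concern.** The economic question is cost per QALY over 6 months in the modified intention-to-treat sample. A woman who leaves early may see other physicians, receive other prescriptions and have a changed quality of life. From a societal perspective, those months belong to the strategy to which she was randomized. The rule stops the diary and the questionnaire when that happens, so no woman in the data set has an observed cost or utility after release. Release is also not a random event: the protocol's own example is an adverse reaction. If one arm has more early releases, the ICER compares one arm measured mostly by observation with another that relies more on imputed months.

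The same sentence limits safety data after release to adverse reactions, that is, to events attributed to a drug. The endpoint in {12} and the rule in {22} ask for adverse events of any kind. One part of the exception also refers to the experimental treatment, which could be read as spironolactone alone.

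**Working it through.** **Plan's own figures.** The plan gives no figure on this point: no release rate, no cost of switching and no utility loss. The nearest is the allowance in {14}: 10% of 91 is 9.1, entered as 9 per group. It reproduces, but it is an allowance for loss to follow-up, not a release rate.

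**Who is affected in the economic analysis.** Under {6b} and {11a}, non-responders are withdrawn only from the M6 visit. By then the 6-month diary and the last EQ-5D used for QALYs are complete. The gap therefore concerns only women released before M6.

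**What imputation can use.** For such a woman, the model can condition on her baseline and pre-release values and on women who remained. It has no observed post-release values from anyone, so the data cannot check how it treats the months after release.

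**Illustrative size (all inputs assumed except the 50,000 euros per QALY in {20b}).** Let d be the between-arm difference in the share released before M6, t the months of the horizon left, g the error in imputed utility, and c the unseen cost per released woman.

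- QALY error per woman = d × (t/12) × g.
  - Low: 0.05 × 2/12 × 0.02 = 0.00017; × 50,000 = 8.3 euros.
  - High: 0.10 × 4/12 × 0.10 = 0.0033; × 50,000 = 167 euros.
- Cost error per woman = d × c.
  - Low: 0.05 × 50 = 2.5 euros.
  - High: 0.10 × 500 = 50 euros.
- A middle case with t = 3, g = 0.05 and c = 200, both errors favouring the same arm: 200 + 0.05 × 0.25 × 50,000 = 825 euros per released woman. With d = 0.05 this is 41 euros per randomized woman; with d = 0.10 it is 83 euros.

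**Scale against sampling error (also assumed).** With a 6-month QALY SD of 0.05 to 0.10 and 100 women per arm, the standard error of the QALY difference is SD × √(2/100) = 0.007 to 0.014. That is about 350 to 700 euros at 50,000 euros per QALY.

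**Safety clauses side by side.**

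- {12}: all AEs and SAEs, to month 12.
- {22}: any adverse event, serious or not.
- {20c}, after release, first part: follow-up of adverse reactions. As worded, this is not tied to an arm.
- {20c}, after release, second part: new adverse reactions associated with the experimental treatment. This phrase occurs only here. Elsewhere ({8}, {14}, {17a}) the word experimental describes the spironolactone arm.

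An unattributed event that starts after release falls under {12} and {22} but not under {20c}. If the second part means spironolactone only, sites could not apply it before M6, because {17a} keeps them blinded until then.

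**The case against.** There are five arguments on the other side.

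- **Imputation and sensitivity analysis are planned, and an article need not describe them fully.** This is fair: no fault lies in the missing detail, and imputation can use pre-release values. But the rule against collecting data is stated, not omitted. A later analysis plan can vary assumptions; it cannot supply values that the protocol says not to collect.
- **The group is small and the error is modest beside sampling noise.** This largely stands. Only releases before M6 count. The middle-case 41 to 83 euros is well below an assumed standard error of 350 to 700 euros. A systematic error is still not reflected in the bootstrap interval.
- **The direction is unknown.** This stands. A reader might infer that the less well tolerated arm has its costs understated and its QALYs overstated. The documents do not support that as a conclusion: a woman who leaves a poorly tolerated drug may have a higher utility than the one imputed.
- **Unequal recording of adverse events is not established.** This also stands. A reader might infer that only reactions to spironolactone are collected after release. The first part of the exception has no arm limit. The experimental treatment may mean either blinded study drug, and blinding before M6 favours that reading. While women are on study, all AEs are collected in both arms.
- **The clause may extend safety collection beyond study exit, not restrict it.** This is possible, since {22} sets no period after exit. But {12} runs to month 12, and the text does not say how released women count towards it.

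**Conclusion.** The point holds in a limited form. For women released before M6, the 6-month societal analysis will have no observed costs or EQ-5D after release, by the protocol's own rule and contrary to the collection schedule in {20b}. If releases differ between arms, the ICER may be biased. The figures of roughly 8 to 167 euros (QALYs) and 2.5 to 50 euros (costs) per woman rest wholly on assumed inputs, including a 5 to 10 point difference in release. They show scale only.

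Separately, the adverse-reactions-only exception is inconsistent with {12} and {22} whichever drug the experimental treatment means, and that term is ambiguous.

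The primary endpoint and the sample size are untouched. This is an inexpensive improvement to a secondary analysis and to the safety wording; it does not threaten the main conclusion.

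**What to change.** 1. **Economic data.** Rewrite the sentence in {20c} so that a woman who stops study treatment without withdrawing consent continues the existing diary and completes EQ-5D at the remaining scheduled time points to M6. Use the observed values, and keep multiple imputation for values that are truly missing.
2. **Safety data.** Reconcile {20c} with {12} and {22}, so that all AEs and SAEs are collected identically in both arms, whatever the attribution, over the period the endpoint covers. If the reference to the experimental treatment is kept, state that it means either study drug. That removes the arm ambiguity, but on its own it does not remove the mismatch with the all-event endpoint.
3. **Sensitivity analysis.** Have the ICER sensitivity analysis in {20b} include departures from missing-at-random for months after release.

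The diary, the questionnaire and the eCRF reporting already exist, and the sample size does not change. The cost is a wording amendment and slight extra follow-up effort at sites.

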### Plans to give access to the full protocol, participant-level data and statistical code {31c}

According to French law, the results of the study will be published on the website of the regulatory authority. Data sharing will be between the investigators only. However, the datasets analysed during the current study will be available from the corresponding author on reasonable request.

## Oversight and monitoring

### Composition of the coordinating centre and trial steering committee {5d}

It has been possible to develop the protocol and carry out the trial thanks to an Executive Committee, which includes a Scientific Committee and a Steering Committee. The Scientific Committee was created and coordinated by [name]. Its membership comprises a biostatistician and methodologist, the study coordinator, the health economist and the project manager of the clinical investigation centre (CIC1413). The Steering Committee is composed of the members of the Scientific Committee with the addition of the data management team, the study nurse who coordinates assistance for patient inclusion in the other centres and the monitoring Clinical Research Assistant (CRA). The Sponsor project manager coordinates this committee and drafts the “FASCE newsletter”, which provides, among other things, the latest news on patient inclusion and amendments to the protocol.

### Composition of the data monitoring committee, its role and reporting structure {21a}

The Data and Safety Monitoring Committee (DSMC) is an advisory committee responsible for reviewing the safety of a clinical trial for the Sponsor and the coordinator of the study. Its members, well-versed in the field of clinical trials (pathology and methodology), are not involved in the study. They are appointed for the duration of the study and undertake to take part in and observe data confidentiality. The members of the DSMC are selected collectively by the coordinator, [name] and the Sponsor. The DSMC is convened at least once a year for safety analysis: the members receive the annual safety report and may be additionally consulted if a suspected unexpected serious adverse reaction (SUSAR) or serious adverse reaction (SAR) involves a specific analytical problem or in the event of any unresolved risk/benefit question arising during the course of the study.

### Adverse event reporting and harms {22}

Side effects reported in clinical trials and case series with spironolactone and the management of acne in women [22] are as follows: (1) the most common side effect in both the clinical trials and case series was menstrual irregularities: 38/264 (14.4%) in the clinical trials and 216/543 (39.8%) in the case series. Thee was no side effect apart from menstrual disturbances with an incidence above 5% in the randomized clinical trials or case series; (2) uncommon side effects (0.1–1.0%) were postural hypotension, depression, diarrhea, muscle pain, increased appetite, drowsiness, rashes/drug eruptions, chloasma-like skin pigmentation, polydipsia, weakness, edema of the legs, change in libido and palpitations. No women were reported to have elevated levels of potassium, and a recent multicentre study of 974 women [52] concluded that routine monitoring of serum potassium in healthy women taking spironolactone for acne is not necessary. Some investigators mentioned that certain side effects were considered beneficial: breast enlargement, reduced symptoms of premenstrual syndrome and less greasy skin and hair. The most frequent adverse reactions to cyclines are photosensitization, gastrointestinal disorders including gastric or esophageal pain, and nausea/vomiting*.*

Any adverse event, whether expected or unexpected, serious or not, must be collected real-time in the study eCRF. All SAEs, whether expected or unexpected, must be reported immediately (on the day of the investigator becoming aware of the event) to the Sponsor through the eCRF. The information mentioned on this form and on attached documents must be complete, accurate, clear (no abbreviations) and coded. Pregnancy, overdose, misuse, medication errors or potential medication errors and quality defects should be notified by the investigator to the Sponsor even if there is no associated adverse reaction.

### Frequency of and plans for trial conduct auditing {23}

An inspection or audit may take place as part of this study, performed by the Sponsor and/or by the regulatory authorities. Inspectors will check the documents, logistics, records and any other resources that the authorities consider to be associated with the clinical trial and that may be located at the trial site itself.

### Plans for seeking research ethics committee/institutional review board (REC/IRB) approval {24}

This clinical study was submitted to and approved by the southwest Ethical Review Board (*Comité de Protection des Personnes Sud-Ouest et Outre-mer III*) on 3 October 2017.

### Plans for communicating important protocol amendments to relevant parties (e.g. trial participants, ethical committees) {25}

The amended protocol should be a dated, updated version. If necessary, the information form and consent form should be amended. The updated protocol is at version 8 on 26 November 2019. All the submissions/declarations were made by the Sponsor Department at CHU Nantes to the French Regulatory Authority (ANSM) and the southwest Ethical Review Board (*Comité de Protection des Personnes Sud-Ouest et Outre-mer III*).

### Statement of who will have access to the final trial dataset, and disclosure of contractual agreements that limit such access for investigators {29}

The investigators will share the entirety of the final trial dataset.

### Disseminations plans {31a}

The trial results will be published in international dermatological, medical and scientific journals and presented at national and international conferences.

### Authorship eligibility guidelines and any intended use of professional writers {31b}

The investigators will follow the rules and guidelines of the International Committee for Medical Journal Editors (ICMJE) [53]. In practice, the Scientific Committee will be among the authors of the publication, as will the investigators who have included the most patients in the trial. The trial Sponsor and the French Ministry of Health, which provided the grant, must be cited in the publication.

## Discussion

Although it has been prescribed for more than 30 years in the USA as an acne treatment in women, spironolactone has no official labelling for acne anywhere in the world, which complicates its use by dermatologists treating this condition. Thus, if we demonstrate the superiority of spironolactone over cycline in the treatment of adult female acne, our randomized trial could have an impact on daily practice, leading the dermatologist to prescribe this treatment with the guarantee of an acceptable benefit/risk balance.

Moreover, beyond the demonstration of the superiority of spironolactone over cycline in the treatment of adult female acne, several collective benefits of this FASCE trial can be envisaged. First, this treatment will greatly improve the quality of life of these patients. This will have social and economic impacts given the substantial social and economic costs of acne vulgaris care. For example, in the USA, acne vulgaris has been responsible for more than 5 million physician visits [54].

Second, as aforementioned, the WHO is worried about the excessive use of antibiotics [31]. This study, if the results are conclusive, will allow physicians to choose spironolactone instead of antibiotics. This saving in antibiotic prescriptions will contribute to reducing the occurrence of antibiotic resistance.

Third, spironolactone can be used as an alternative to isotretinoin in women and this is of particular interest for two reasons: first, isotretinoin is associated with a strict programme of contraception that is often difficult for patients to follow; second, the peripheral hyperandrogenia that frequently occurs in women does not respond well to isotretinoin, with frequent relapses.

In view of all the potential benefits and impacts of this study, its results are eagerly awaited by dermatologists, and in particular by private dermatologists, who see these women suffering from acne in their clinical practice.

## Trial status

This trial is still ongoing; patient inclusion is not yet complete.

The updated protocol is version 8 on 26 November 2019.

The first patient was included on 31 January 2018.

Recruitment by the investigating centres is planned to continue until 30 June 2021.

## Data Availability

Data sharing is not applicable to this paper as no datasets were generated or analysed during the current study. The data from the completed trial will not be shared and will only be transmitted to the Sponsor. Data collected during the test may be processed electronically, in accordance with the requirements of CNIL (compliance with reference methodology MR001).

## Abbreviations

ACE: Angiotensin-converting enzyme
AFAST: Adult Female Acne Scoring Tool
ANSM: Agence Nationale de Sécurité du Médicament et des produits de santé
AR: Adverse reaction
ASR: Annual Safety Report
CADI: Cardiff Acne Disability Index
CEA: Cost-effectiveness analysis
CNIL: Commission Nationale de l’Informatique et des Libertés
CRA: Clinical Research Associate (monitor)
CRF: Case report form
DHEAS: Dehydroepiandrosterone
DHT: Dihydrotestosterone
DSMC: Data and Safety Monitoring Committee
ECLA: Echelle de cotation des Lésions d’Acné
eCRF: Electronic case report form
EQ-5D: Euroqol-5 dimensions questionnaire
GAGS: Global Acne Grading System
GCP: Good Clinical Practice
GEA: Global Evaluation Assessment
ICER: Incremental cost-effectiveness ratio
IGF 1: Insulin-like growth factor 1
IUD: Intra-uterine device
LH: Luteinizing hormone
NSAID: Non-steroidal anti-inflammatory drug
OC: Oral contraceptive
QALY: Quality-adjusted life year
QoL: Quality of life
RCT: Randomized controlled trial
SAE: Serious adverse event
WHO: World Health Organisation
